##### Secondary outcome

All GPs participating will be posted a questionnaire when all patients have been included. This questionnaire will primarily be designed to evaluate the GPs. satisfaction with the new software, focusing on areas such as user friendliness and time consumption.

##### Logistics

For patients who are included, the GP must follow certain steps to avoid trial bias. However, it is important that the procedures for enrolling patients in the trial are not so time-consuming that GPs choose not to include patients. The steps in the inclusion process will be:

1. Identify patients who meet the inclusion criteria according to guidelines provided in the electronic health record.

2. Obtain written informed consent from all eligible patients.

3. Call the randomisation centre at the University Hospital. The patient is then registered in the study database and thereby automatically randomised to either the one-stop approach or the traditional patient pathway.

4. If the patient is randomised to the intervention group, the standardised referral forms provided by the electronic health record must be used. If the patient is randomised to the control group, the traditional referral forms (also provided y the electronic health record) with no mandatory information regarding the specific disease must be used.

5. If randomised to the intervention group: book place, time and date of surgery

6. Print the information form about the surgical procedure and where and when to meet for surgery and give to the patient.

##### Sample size

To calculate the sample size needed, we identified all patients who had undergone the specified surgical procedures within three months of normal surgical activity (September, October and November 2007). Of these 33 patients, 22 patients could be included in a one-stop protocol. The rest of the patients were not eligible due to different patient pathways.

We calculated the average waiting time from referral to examination at the surgical outpatient dept, the waiting time from outpatient examination to surgery, and the total waiting time (Table 2).

**Table 2 T2:** Mean waiting time for examination and surgical treatment for selected day case prcedures at a University Hospital during a three-month period of normal activity.

	GP referral to examination at the surgical outpatient clinic (days)	Internal hospital referral to day case surgery (days)	Total waiting time (days)
Waiting time^a ^(mean)	122	119	241
Standard deviation	118	92	154

^a ^Inguinal hernia, pilonidal sinus and uncomplicated gallstone disease

Based upon calculations in Table 2, we assume that there is no significant difference in waiting time between the three groups. Alpha and beta were set at 0.05 and 0.2 respectively. We estimate that a significant decrease in mean waiting time for surgery would be 60 days. The standard deviation is estimated as 120 days. We assume an exclusion rate of 20%, so that a sample size of 60 patients in each group is required.

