##### Patients

Patients are eligible if they have been diagnosed by their GP for an inguinal hernia, sinus pilonoidalis or gallstone disease requiring surgical treatment. Patients with medical conditions making them unfit for outpatient surgery who are admitted to the surgical department prior to surgery are not eligible. In 2007, 366 patients were surgically treated at the Day Case Surgical Department for these three conditions. Patients will be included after giving written informed consent.

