#### Analysis

Treatment arms will be compared with respect to potential covariates using continuous and categorical variables. This will include variables related to patients (sex, age, type of disease, date of referral, date of outpatient examination, date of outpatient surgery), cost (patient sick leave, GP examination, hospital administration, surgical outpatient examination, surgical outpatient treatment, unused surgical capacity due to incorrect referral, patient travel cost). The results will be presented as intention-to-treat analyses and treatment analyses.

We will conduct analyses using the latest version of SPSS. The trial will be reported according to the CONSORT standards for reporting randomised trials [6,7].

The results will be expressed as an odds ratio (for binary outcomes), hazard ratio (time to event outcomes) or mean difference (for continuous outcomes) with corresponding standard errors, 95% confidence intervals and associated p-values. For all two-sided tests we use alpha = 0.05 level of significance.

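### The trial is sized on an SD of 120 days although its own pilot table gives 154 for total waiting time; with 48 evaluable per group, two-sided power for 60 days is about 47% to 72%, not 80%

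*Protocol article*

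**What the plan says.** The Sample size section of the protocol extracts waiting times from patients operated on in three months of 2007 in order to size the trial, and reports them in Table 2 ("Mean waiting time for examination and surgical treatment for selected day case prcedures at a University Hospital"). The columns are referral to clinic, clinic to surgery, and total. The means are 122, 119 and 241 days, and the SD row reads "Standard deviation 118 92 154".

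The calculation that follows has these elements:

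- Error rates: "Alpha and beta were set at 0.05 and 0.2 respectively".
- Target difference: "We estimate that a significant decrease in mean waiting time for surgery would be 60 days".
- Variability: "The standard deviation is estimated as 120 days".
- A 20% exclusion rate, leading to 60 patients per group.

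The Primary outcome section measures waiting time from the referral's entry in the hospital record to the date of surgery. This corresponds to the total column of Table 2. The Sample size section does not say whether the test is one- or two-sided. The Analysis section says "For all two-sided tests we use alpha = 0.05 level of significance" and announces no one-sided test.

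**The concern.** The 60-day target is scaled to the total waiting time: the Abstract calls it 25%, and 60/241 = 24.9%. The SD set against it is not the one that Table 2 gives for that total, and nothing explains the change. Required sample size grows with the square of the SD, so moving from 120 to 154 multiplies it by (154/120)² = 1.65.

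This is the only sample-size basis in the protocol, and it concerns a primary endpoint. If power is well below 80%, the trial could report no significant reduction when a real 60-day gain exists.

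**Working it through.** **Inputs.** Difference 60 days, alpha 0.05, power 0.80, SD 120, exclusions 20% and 60 per group come from the Sample size section. SD 154 comes from Table 2. Two-sided testing is taken from the Analysis section. Evaluable patients: 60 × 0.8 = 48 per group.

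**1. Reproducing the plan's 60 per group (SD 120).** Formula: n = 2(z_alpha + z_beta)²(SD/60)².

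- Two-sided: 2 × 7.849 × (120/60)² = 62.8, so 63. Allowing for exclusions: 63/0.8 = 79, or 63 × 1.2 = 76. Neither gives 60.
- One-sided: 2 × (1.645 + 0.842)² × 4 = 49.5, so 50. Then 50/0.8 = 63, or 50 × 1.2 = 60.

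Of these four combinations, only one-sided alpha with multiplication by 1.2 gives 60. Multiplying by 1.2 does not restore the required number: 60 less 20% leaves 48, not 50.

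**2. Is 154 consistent within Table 2?** If the two legs were independent, the SD of the total would be √(118² + 92²) = 150. A value of 154 implies a correlation of (154² − 118² − 92²)/(2 × 118 × 92) = 0.06. So 154 fits the other two columns and does not look like a misprint.

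**3. Power for 60 days, two-sided 0.05.** Normal approximation: power = Φ(60/SE − 1.96), with SE = √[(SD_control² + SD_one-stop²)/n]. For example, with SD 154 in both arms and n = 48, SE = 154 × √(2/48) = 31.4, 60/31.4 = 1.91, and Φ(1.91 − 1.96) = 48%. The t-test gives 47%.

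| SD control / one-stop | 48 evaluable per group | 60 evaluable per group |
|---|---|---|
| 120 / 120 | 69% (t-test 68%) | 78% (t-test 78%) |
| 154 / 154 | 48% (t-test 47%) | 57% (t-test 56%) |
| 154 / 120 | 57% | 66% |
| 154 / 92 | 64% | 74% |
| 154 / 53 | 72% | 81% |

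The last three rows use the normal approximation. Their one-stop SDs are assumptions: 120 is the plan's figure, 92 is the SD of the surgery leg in Table 2, and 53 is derived under the objection below.

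**4. Size needed and detectable difference if SD 154 applies to both arms.** n = 2 × 7.849 × (154/60)² = 103.4, so 104 evaluable per group (105 by t-test). Dividing 104 by 0.8 gives 130 randomised per group. With 48 evaluable per group, the difference detectable at 80% power is (1.960 + 0.842) × 154 × √(2/48) = 88 days, or 89 days by t-test. That is 89/241 = 37% of the mean, against the stated 25%.

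**5. Splitting the shortfall.** With SD 120, two-sided testing and 48 evaluable, power is already about 68%, so about 12 points are lost to sidedness and the exclusion allowance. Raising the SD to 154 in both arms takes it from about 68% to about 47%, a further 21 points.

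**The case against.** The strongest reply is that Table 2 describes only the traditional two-leg pathway. The one-stop arm has no clinic leg, and the Intervention section offers surgery slots over a 6-month period. If every patient is operated on at the booked time, the wait lies within about 0 to 183 days. Its SD then cannot exceed about 183/2 = 91 days, and a uniform spread would give 183/√12 = 53. Combined with 154 in the control arm, the root-mean-square SD is √[(154² + 53²)/2] = 115 to √[(154² + 91²)/2] = 126, which brackets 120. This stands as a reason not to read 47% as the trial's actual power; that figure needs SD 154 in both arms. But the protocol does not make the argument, rescheduling or cross-over would widen the one-stop spread, and power at 48 evaluable still stops at about 72%. It reaches 80% (81%) only with one-stop SD 53 and no exclusions at all.

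A one-sided calculation may have been intended. At 48 evaluable per group it gives 78% to 79% with SD 120, but only 60% with SD 154 in both arms, and the Analysis section does not announce a one-sided test.

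Three further inferences are tempting but not supported:

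- *That the pilot data rule out 120.* If Table 2 rests on 22 patients ("Of these 33 patients, 22 patients could be included in a one-stop protocol"), which the text does not say outright, and if waiting times are normal, the 95% interval for the SD is 154 × √(21/35.48) = 118 to 154 × √(21/10.28) = 220. It includes 120, though near its favourable end.
- *That 120 was taken from the first leg's 118.* The document does not say so, and other routes also land near 120: the mean of the three SDs in Table 2 is (118 + 92 + 154)/3 = 121.
- *That the pilot sample is biased.* The Patients section says "In 2007, 366 patients were surgically treated at the Day Case Surgical Department for these three conditions", or 366/4 = 91.5 per quarter against 33 in the pilot. The two counts may differ in procedures or sites, and the gap does not show that the SD is wrong in either direction.

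**Conclusion.** The point holds: the SD used in the calculation departs without explanation from the SD that the same section reports for the primary endpoint, and the stated 80% power is not supported. At 48 evaluable per group and two-sided 0.05, every scenario examined falls short: about 68% at the plan's own SD, about 47% with 154 in both arms, and about 57% to 72% with 154 in the control arm and an assumed one-stop SD of 120 down to 53.

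The SD is not the sole cause, because the sidedness and the exclusion allowance already lower power at SD 120. The range rests on a comparison of means, a 60-day difference, the full 20% exclusion rate, and assumed one-stop SDs that the document does not supply. It does not establish that 120 is impossible. It shows that 120 is unjustified and that the sample size does not follow from it under two-sided testing.

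**What to change.** Recalculate with the Table 2 SD of 154 for the control arm and a stated, justified SD for the one-stop arm. Use two-sided 0.05, and allow for exclusions by dividing by (1 − 0.2). State the sidedness and the formula in the Sample size section. Then restate the power for 60 days, or the detectable difference at 80% power, for 120 patients, shown over the range of plausible SDs; the detectable difference is about 89 days if 154 applies to both arms. If 120 is kept as an average over the two arms, give the arm-specific SDs behind it.

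Optionally, refine the control SD from eligible patients among those treated in 2007, using dates already in the hospital record, and say how the count of 33 relates to the annual 366.

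The cost is a short recalculation and new wording, plus a further record extraction if the SD is refined. The downside is a less favourable stated power.

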**Materials and Methods:**

In a randomised controlled trial, selected patients (inguinal hernia, gallstone disease and pilonidal sinus) referred to the university hospital are either randomised to direct electronic referral and booking for outpatient surgery (one stop), or to the traditional patient pathway where all patients are seen at the outpatient clinic several weeks ahead of surgery.

Consultants in gastrointestinal surgery designed standardised referral forms and guidelines. New software has been designed making it possible to implement referral forms, guidelines and patient information in the GP's electronic health record. For "one-stop" referral, GPs must provide mandatory information about the specific condition. Referrals were linked to a booking system, enabling the GPs to book the hospital, day and time for outpatient surgery. The primary endpoints are waiting time and costs. The sample size calculation was based on waiting time. A reduction in waiting time of 60 days (effect size), 25%, is significant, resulting in a sample size of 120 patients in total.

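### Sixty patients per group does not give 80% power for the plan's own inputs: with the two-sided 5% test and the assumed 20% exclusions, power is about 68%

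*Protocol article*

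**What the plan says.** The Sample size section gives a complete set of inputs. On error rates: "Alpha and beta were set at 0.05 and 0.2 respectively". On the effect: "We estimate that a significant decrease in mean waiting time for surgery would be 60 days". On variability: "The standard deviation is estimated as 120 days". It then concludes: "We assume an exclusion rate of 20%, so that a sample size of 60 patients in each group is required". The Materials and Methods part of the abstract says that the calculation rests on waiting time, one of the two primary endpoints, and carries the figure forward: "resulting in a sample size of 120 patients in total".

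The Sample size section does not say whether the test is one-sided or two-sided. The Analysis section says "For all two-sided tests we use alpha = 0.05 level of significance" and promises 95% confidence intervals. No one-sided test is mentioned anywhere in the article.

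**The concern.** The difference is half a standard deviation (60/120 = 0.5). At that effect size, a two-sided 5% comparison with 80% power needs a little over 60 evaluable patients per group, so a figure of 60 that already includes a 20% allowance for exclusions cannot be right.

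The stated power governs how a null result is read. A non-significant difference in waiting time would be taken as coming from a trial with a 20% chance of missing a 60-day reduction. If the true chance is nearer one in three, that reading is unjustified, and readers of the article cannot tell.

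**Working it through.** **Inputs**

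- Difference 60 days, SD 120 days, alpha 0.05, beta 0.2, exclusions 20%, 60 per group: Sample size section.
- Two-sided testing: Analysis section.
- Equal allocation: implied by 60 in each group and 120 in total.

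**Step 1. Trying to reproduce 60 per group**

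Normal approximation: n per group = 2 × (z for alpha + z for power)² × (SD/difference)², with (120/60)² = 4.

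- Two-sided 5%: 2 × (1.960 + 0.842)² × 4 = 62.8, so 63 (t-test: 63.8, so 64).
- One-sided 5%: 2 × (1.645 + 0.842)² × 4 = 49.5, so 50 (t-test: 50.2).

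If a fraction 0.2 of those randomised is lost, the number to randomise is n/(1 − 0.2). Multiplying by 1.2 is a common shortcut that falls short: 20% lost from 1.2n leaves only 0.96n.

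| Test | Evaluable per group | n/0.8 | n × 1.2 |
|---|---|---|---|
| Two-sided 5% | 63 (t: 64) | 79 (t: 80) | 76 (t: 77) |
| One-sided 5% | 50 | 63 | 60 |

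Of these routes, only a one-sided test combined with the × 1.2 shortcut gives 60. The article states neither step, so this is a possible explanation of the number and not a record of how it was obtained. Under two-sided testing, 60 is below the requirement before any exclusions, so no method of inflation can produce it.

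**Step 2. Power of the stated design**

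Evaluable patients after 20% exclusions: 60 × 0.8 = 48 per group.

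Standard error of the difference: 120 × √(2/48) = 24.5 days. Then 60/24.5 = 2.449, and 2.449 − 1.960 = 0.489, which gives a normal-approximation power of 68.8%. The other cases follow in the same way.

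| Evaluable per group | Test | Power, normal | Power, t-test |
|---|---|---|---|
| 48 | two-sided 5% | 68.8% | 67.9% |
| 60 (no exclusions) | two-sided 5% | 78.2% | 77.5% |
| 48 | one-sided 5% | 78.9% | 78.4% |

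**Step 3. Difference detectable with 80% power at 48 per group, two-sided**

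Normal approximation: (1.960 + 0.842) × 24.5 = 68.6 days. By t-test: 69.3 days.

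**Step 4. Is there a hidden margin in the SD?**

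For 48 per group to reach 80% two-sided power for 60 days, the SD would have to be 60 × √(48/2)/(1.960 + 0.842) = 105 days, which is below the 120 assumed. Table 2 reports 154 days for total waiting time. With 154, power at 48 per group would be about 47% to 48%. The conclusion does not use this figure, but it shows that the stated SD is not a cautious choice that offsets the shortfall.

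**The case against.** The best defence concerns sidedness. The Sample size section does not state it, the hypothesis is worded as a decrease in waiting time, and the Analysis sentence could be read as setting the level only for whichever tests happen to be two-sided. On a one-sided 5% test, power at 48 per group is 78.4%, a trivial shortfall. What stands is that two-sidedness comes from the Analysis section and not from the sample size paragraph. But a directional hypothesis does not make a test one-sided, the article names no one-sided test, and it promises 95% intervals. Two-sided is the natural reading, and even the one-sided reading does not quite reach 80% after the exclusions.

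A second defence is that the 68% needs the full 20% loss. The term exclusion is not defined, and intention-to-treat analyses are planned. If all 60 per group were analysed, power would be 77.5%, about 3 to 4 patients per group short. That is fair as a description of the range. However, the sentence presents 60 as already containing the allowance, so 48 evaluable is what the plan itself implies. If 60 were meant as evaluable patients, the number to randomise would be 60/0.8 = 75 per group, or 150, which contradicts the 120 in the abstract.

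Third, the Analysis section lists a hazard ratio as well as a mean difference, and randomisation is stratified by diagnosis, so the eventual analysis may not be an unadjusted t-test. That is true, but the sample size inputs are a difference in means and an SD, and the two-sample comparison is the right check on them.

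**Conclusion.** The concern holds. For a two-sided 5% test with the plan's own difference, SD and beta, 63 to 64 evaluable patients per group are needed. The stated 60 falls short before exclusions and well short after them. The design as written has about 68% power for a 60-day difference, which means a 32% chance of missing it against the 20% claimed.

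This rests on three assumptions: two-sided testing as in the Analysis section, a 20% loss that leaves 48 evaluable per group, and an SD of 120 days. If no patient is excluded, the shortfall shrinks to 2.5 percentage points. The explanation by a one-sided test and a × 1.2 inflation is only an inference, and the conclusion does not depend on it.

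**What to change.** Correct the Sample size section so that the number, the sidedness and the power agree, and make the abstract match. Suggested content: with 120 patients randomised and 20% excluded (48 evaluable per group), a two-sided 5% test has about 68% power for a 60-day difference, or 80% power for a difference of about 69 days, assuming an SD of 120 days. State that this is conditional on the SD, and give the reason for using 120 when Table 2 shows 154 for total waiting time.

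The cost is rewording and a less favourable power figure. No extra patients are needed.

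If the sponsor prefers to keep 80% power for 60 days, the target becomes about 80 per group, 160 in total, which is 40 more than planned.

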#### Randomisation

Patients will be randomised at the time of referral by the GP. The randomization service is telephone-based and managed by the University Hospital. Patients are stratified into three groups according to their diagnosis.

#### Blinding

To avoid bias, surgeons and administrative personnel are blinded to patients' status in the trial. Referrals of pilonidal sinus, gallstone disease and inguinal hernia to the surgical outpatient clinic will be examined by the principal investigator. The examining and operating surgeon at the surgical department will be blinded to all data concerning the one-stop trial. Patients enrolled in the trial will be mixed with patients referred to the surgical outpatient department by GPs not participating in the trial.

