## Background

The shift from inpatient to outpatient care is drawing attention to the role of the outpatient clinic and day case surgery. An increased focus on cost benefit and waiting time for examination and treatment of surgical patients has made it necessary to develop new strategies for referral routines and the patient flow between primary and secondary care. One-stop day case surgery, i.e. day case surgery based upon standardised referrals, may be a solution for selected surgical patients [1,2].

In Norway, all patients with an inguinal hernia, gallstones, or pilonidal sinus are primarily examined by a general practitioner (GP). The GP performs a regular clinical examination, and they refer the patient to examination at the surgical outpatient clinic, at the same time forwarding supplemental clinical information about the patient (i.e. age, sex, social status, other diseases and clinical conditions, medication). The referrals are not standardised. Within three weeks, a hospital doctor must read the referral and draw up a treatment or investigation plan. A time schedule for the outpatient clinic examination is proposed on the basis of the information in the referral and the availability of appointments for examinations. All patients are then examined by a surgeon at the outpatient clinic, who in turn refers the patient to outpatient surgery. This in-hospital referral must be read and prioritised by a senior hospital surgeon within two weeks before a final schedule for an operation for the patient is decided.

According to the Norwegian Directorate for Health and Social Affairs, patients with inguinal hernia must wait up to 22 weeks for an examination by a gastrointestinal surgeon at a surgical outpatient clinic, and up to 28 weeks for day case outpatient surgery (Table 1) [3]. Similar or even longer waiting times apply to conditions such as symptomatic gallbladder stones and pilonidal sinus.

**Table 1 T1:** Waiting time reported by the Norwegian Directorate for Health and Social Affairs for surgical outpatient examination and surgery in Norway, February 2008 [3].

	Outpatient Consultation (weeks)	Outpatient Surgery (weeks)
Gallstones	2–22	2–30
Inguinal hernia	2–22	2–28
Pilonidal sinus	2–30	2–48

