##### Intervention

The one-stop strategy is a set of interventions directed at GPs referring patients to the University Hospital. The interventions include: Guidelines for referral, standardised electronic referrals, booking for outpatient surgery and a patient information form.

Guidelines for referral: Guidelines for inguinal hernia, sinus pilonoidalis and gallstone disease were developed (Figure 3). All surgeons performing the surgical procedures reviewed the giudelines, and after a three-month period consensus was reached. The guidelines consisted of signs and symptoms for the condition, indications and contraindications for surgery, necessary blood samples and radiological examinations prior to surgery (for gallstone disease). Photographs of the condition were included in the guidelines for sinus pilonoidalis and inguinal hernia. These guidelines were implemented in the GPs electronic health record.

Standardised referral forms: Standardised referral forms were developed by specialists in gastrointestinal surgery in cooperation with GPs (Figure 2). These referral forms consisted of three parts: information needed for anaesthesia (mandatory), information needed for surgeons (mandatory) and additional information provided by the GPs. These referral forms were implemented in the GPs' electronic health records (Profdoc Winmed).

Booking of time, date and hospital for surgery: The booking system is integrated in the electronic health record (Profdoc Winmed); booking is done at the same time as referral. Patients can choose the optimal time and hospital for surgery. The system is managed by the Day Case Surgical Department. Available times and locations for surgery during a 6-month period are presented. Surgical capacity that has not been booked within two weeks of the relevant date is withdrawn and offered to patients who are not participating in the trial.

Patient information form: A patient information form (printable, integrated in the electronic health record) was prepared by a specialist in gastrointestinal surgery. The form included information about the place and time for surgery, information about the surgical procedure, and advice for the patient following surgery. Information about possible complications of surgery was also provided.

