#### Control arm

The control group consists of patients randomised to use the regular patient pathway prior to day case outpatient surgery. All these patients are referred to the surgical outpatient clinic. At the outpatient clinic patients are examined by a surgeon, who determines whether surgery is indicated. If so, patients are referred to outpatient surgery and the surgical procedure is performed several weeks after the examination.

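### The principal investigator, not stated to be blinded, examines clinic referrals among which the only trial patients are controls, so the first leg of the control wait may be open to investigator influence

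*Protocol article*

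**What the plan says.** The Blinding section opens with the aim of avoiding bias and says that "surgeons and administrative personnel are blinded to patients' status in the trial". It then states: "Referrals of pilonidal sinus, gallstone disease and inguinal hernia to the surgical outpatient clinic will be examined by the principal investigator". It goes on to blind the examining and operating surgeon. The principal investigator is not named among those blinded. The remaining safeguard is: "Patients enrolled in the trial will be mixed with patients referred to the surgical outpatient department by GPs not participating in the trial".

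The Background describes the regular pathway: "Within three weeks, a hospital doctor must read the referral and draw up a treatment or investigation plan". On what follows from that reading it says: "A time schedule for the outpatient clinic examination is proposed on the basis of the information in the referral". The same sentence adds that appointment availability also counts. The second, in-hospital referral is read and prioritised by a senior hospital surgeon.

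The Control arm section defines the comparator: "The control group consists of patients randomised to use the regular patient pathway prior to day case outpatient surgery". It adds: "All these patients are referred to the surgical outpatient clinic". For the one-stop arm, the Intervention section says that "booking is done at the same time as referral", in a system run by the Day Case Surgical Department.

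Under Primary outcome, waiting time is built from the date the referral is noted in the hospital record, the date of outpatient examination (controls only) and the date of surgery.

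**The concern.** Three features of the design combine.

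- **Position.** In the regular pathway, the person who reads the referral stands upstream of the clinic date. The clock for the primary outcome starts when the referral is noted in the hospital record, so time spent waiting to be read, and the priority then given, fall inside the measured interval.
- **One-sidedness.** All controls pass through this set of referrals and, by design, no one-stop patient does. Faster or slower handling can move the control mean but has no counterpart in the intervention arm.
- **Blinding.** The person placed there is the one testing the hypothesis, and the text neither states that this person is blinded nor limits the role.

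Two things are at stake. The primary comparison could be shifted in either direction: slower handling would exaggerate the benefit of one-stop, and faster handling would hide it. The control arm might also no longer represent the regular pathway it is declared to be. Neither effect needs bad faith, or recognition of any individual trial patient.

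**Working it through.** **Step 1. Who is exposed.** Taken together, the Blinding, Control arm and Intervention sections give:

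| | One-stop arm | Control arm |
|---|---|---|
| Referred to the outpatient clinic | No; GP books surgery at referral | Yes, all |
| Referral among those the investigator examines | No, by design | Yes |
| Clinic interval inside the primary outcome | No | Yes |

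**Step 2. Share of the control wait after the referral.** Inputs are the pilot means in Table 2 (Sample size section; 22 patients could have been included in a one-stop protocol).

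- Total: 122 + 119 = 241 days, which reproduces the stated total.
- First leg, referral to examination: 122/241 = 50.6%.
- Second leg, examination to surgery: 119/241 = 49.4%. A senior hospital surgeon reads the referral for this leg, so it is not assigned to the investigator.

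The 50.6% is the share exposed, not a bias estimate. It is an upper bound because appointment availability also fixes the date.

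**Step 3. The one reading interval the article bounds.** Three weeks = 21 days.

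- Share of the total pilot wait: 21/241 = 8.7%.
- Share of the 60-day target difference: 21/60 = 35%.

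A shift of the full 21 days would require one reader to use the whole window and the other none of it, with each day carried through to the clinic date. It is an extreme for this interval.

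**Step 4. What such a shift would do (illustration; the shift is assumed).** Inputs: planning SD 120 days and 60 per group (Sample size section), or 60 × 0.8 = 48 per group after the 20% exclusion; two-sided alpha 0.05. Let b be the shift in the control mean, with no true effect.

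- SE = 120 × √(2/n): 24.5 days for n = 48 and 21.9 days for n = 60.
- Rejection rate = 1 − Φ(1.96 − b/SE) + Φ(−1.96 − b/SE).

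| Assumed shift b | Share of 60 days | Rejection rate, n = 48 | Rejection rate, n = 60 |
|---|---|---|---|
| 12.2 days (10% of the first leg) | 20% | 7.9% | 8.6% |
| 21 days (whole reading window) | 35% | 13.8% | 16.0% |
| 30.5 days (25% of the first leg) | 51% | 23.8% | 28.5% |

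The nominal rate is 5%. The 10% and 25% shifts have no source in the article; they only show a range. In the other direction, with a true difference of 60 days, control handling that is 21 days quicker would leave an apparent difference of 60 − 21 = 39 days.

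**The case against.** The strongest reply is that the text says only that referrals are examined. It does not say that the investigator prioritises them, proposes the clinic date or displaces the usual reader. The word could mean screening to identify trial patients or check eligibility. The investigator could also be one of the hospital doctors who ordinarily read these referrals. A reader might infer that the comparator is definitely not regular triage. The article does not support that: whether this step replaces or adds to ordinary reading is left open. This part of the reply stands.

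A reader might also infer that the investigator controls half of the control wait. That is not supported either. Appointment availability also sets the date, and nothing gives the investigator control of clinic capacity. Where capacity is the limit, reordering within the referrals is largely zero-sum, so the control mean need not move unless controls are singled out. This stands as well, and it is why 122 of 241 days can only be an upper bound.

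Finally, mixing with patients of non-participating GPs makes controls harder to single out. It does limit selective handling. It does not reach a general change in how the referrals for these three diagnoses are handled, because the only trial patients such a change could affect are controls. The objection narrows the point without removing it. This is not merely detail that a condensed article omits: the arrangement is stated, is offered as protection against bias, and as worded places an investigator not said to be blinded where one arm's primary outcome may be affected.

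**Conclusion.** The point holds in conditional form. As written, the principal investigator may influence the first leg of the control arm's waiting time, and the control pathway may differ from regular triage. The exposure is one-sided by design.

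Its size is uncertain. At most 122 of 241 pilot days (50.6%) lie in the exposed leg, and the only reading interval the article bounds is up to 21 days, or 35% of the target difference. The actual shift may be zero, and its direction is unknown.

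This rests on three assumptions: that examining a referral can affect its priority or date, that the 2007 pilot means describe the trial's control pathway, and that one-stop patients do bypass the clinic as designed. The change is worth making because it closes the route if the investigator triages, and costs almost nothing if the role was only screening.

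**What to change.** State in the Blinding section that clinic referrals for the three diagnoses are read, prioritised and scheduled by the hospital doctors who normally do this, without knowledge of trial status. State that the principal investigator sees a referral only after its priority and clinic date are recorded, solely to identify trial patients or check eligibility, and may not alter either. If the investigator is normally one of these readers, have other usual readers handle these diagnoses during the trial.

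Report the two legs of the control wait separately. The required dates are already collected, and the first leg can then be set against the pilot mean of 122 days, with the caution that the pilot is small.

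The cost is a short addition to the text, slightly later sight of referrals for the investigator and, if the investigator is a usual reader, some redistribution of triage work.
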